## Conditions

Conditions: Walking

Keywords: brisk walking  
Tai Chi Chuan  
combine  
health- related physical fitness  
health parameter

## Study Design

Study Type: Interventional

Primary Purpose: Treatment

Study Phase: N/A

Interventional Study Model: Factorial Assignment

There are four groups, 1 control group, and 3 intervention groups. Three intervention groups include the brisk walking group, the Tai Chi Chuan group, and their combination group.

Number of Arms: 4

Masking: None (Open Label)

Try not to allow communication and contact between participants in each group. Researchers do not participate in training. Researchers do not disclose more research information. Data collection and entry should be operated by professional personnel.

Allocation: Randomized

Enrollment: 100 [Actual]

## Arms and Interventions

| Arms                                                                                                                                                                                                                                                                                                                                                                                                                                                                                                                                                                               | Assigned Interventions                                                                                                                                                                                                                                                                                                                                                                                                                                                                                                                                      |
|------------------------------------------------------------------------------------------------------------------------------------------------------------------------------------------------------------------------------------------------------------------------------------------------------------------------------------------------------------------------------------------------------------------------------------------------------------------------------------------------------------------------------------------------------------------------------------|-------------------------------------------------------------------------------------------------------------------------------------------------------------------------------------------------------------------------------------------------------------------------------------------------------------------------------------------------------------------------------------------------------------------------------------------------------------------------------------------------------------------------------------------------------------|
| 
Experimental: Brisk walking group
 Type of exercise is brisk walking. The duration of each exercise is from 35 minutes to 60 minutes, with 5 minutes of training time added every two weeks.
 
The frequency of each exercise is 3 times a week. Total exercise time is 12 weeks. The intensity is 50%-70% of the individual's maximum heart rate, gradually increasing the intensity over time.
                                                                                                                                                            | 
Behavioral: Brisk walking and Tai Chi Chuan
 This study includes four groups, the three experimental groups are brisk walking group, Tai chi chuan group, brisk walking combined with Tai chi chuan group, and control group. Among the three experimental groups and exercise time, exercise intensity and exercise frequency are the same over time.
 
Other Names:
 
 
• Tai Chi Chuan (only#)
 
• Brisk walking (only)
 
• Tai Chi Chuan combined with brisk walking
 
 |
| 
Experimental: Tai Chi Chuan
 Type of exercise is Tai Chi Chuan. The duration of each exercise is from 35 minutes to 60 minutes, with 5 minutes of training time added every two weeks.
 
The frequency of each exercise is 3 times a week. Total exercise time is 12 weeks. The intensity is 50%-70% of the individual's maximum heart rate.
                                                                                                                                                                                                                | 
Behavioral: Brisk walking and Tai Chi Chuan
 This study includes four groups, the three experimental groups are brisk walking group, Tai chi chuan group, brisk walking combined with Tai chi chuan group, and control group. Among the three experimental groups and exercise time, exercise intensity and exercise frequency are the same over time.
 
Other Names:
 
 
• Tai Chi Chuan (only#)
 
• Brisk walking (only)
 
• Tai Chi Chuan combined with brisk walking
 
 |
| 
Experimental: Brisk walking combined with Tai Chi Chuan
 Type of exercise is brisk walking combine with Tai Chi Chuan. The duration of each exercise is from 35 minutes to 60 minutes, with 5 minutes of training time added every two weeks.
 
The frequency of each exercise is 3 times a week. Total exercise time is 12 weeks. The intensity of brisk walking is 50%-70% of the individual's maximum heart rate, gradually increasing the intensity over time.
 
The intensity of Tai Chi Chuan is 50%-70% of the individual's maximum heart rate.
 | 
Behavioral: Brisk walking and Tai Chi Chuan
 This study includes four groups, the three experimental groups are brisk walking group, Tai chi chuan group, brisk walking combined with Tai chi chuan group, and control group. Among the three experimental groups and exercise time, exercise intensity and exercise frequency are the same over time.
 
Other Names:
 
 
• Tai Chi Chuan (only#)
 
• Brisk walking (only)
 
                                                      |

| Arms                                                        | Assigned Interventions                      |
|-------------------------------------------------------------|---------------------------------------------|
|                                                             | • Tai Chi Chuan combined with brisk walking |
| No Intervention: Control Group
Keeping their daily life. |                                             |

## Outcome Measures

### Primary Outcome Measure:

1. Body composition measurement by Waist circumference

Measuring process: The measuring ruler should be a cocoa-curved but inelastic tape ruler. The ruler should be placed on the surface of the skin and should not be pressed against the subcutaneous fat tissue. If you use Gulick elastic handle, its handle can be extended to the same mark every time. The same part should be measured twice. If the difference between the two measurement results is more than 5mm, the scene should be measured again.

[Time Frame: 5 minutes]

2. Flexibility measurement by sit and reach test

The sit and reach test is a common measure of flexibility, and specifically measures the flexibility of the lower back and hamstring muscles. Seated forward bend test instrument to measure.

[Time Frame: 5 minutes]

3. Flexibility measurement by Back Scratch Test

The Back Scratch Test, or simply the Scratch Test, measures how close the hands can be brought together behind the back.

Use a meter to measure the overlapping part of your hands.

[Time Frame: 5 minutes]

4. Muscular strength measurement chair stand test

The chair stand test is similar to a squat test to measure leg strength, in which participants stand up repeatedly from a chair for 30 seconds.

The chair stand test is similar to a squat test to measure leg strength, in which participants stand up repeatedly from a chair for 30 seconds.

equipment required: a straight back or folding chair without arm rests (seat 17 inches/44 cm high), stopwatch

[Time Frame: 5 minutes]

5. Muscular strength measurement by Arm Curl test

The aim of this test is to do as many arm curls as possible in 30 seconds. equipment required: 4 pound weight (women, AAHPERD), 5 pound weight (women, SFT). A chair without armrests, stopwatch.

[Time Frame: 5 minutes]

6. Muscle endurance measurement by knee push-up

1. The push-up fitness test (also called the press-up test) measures upper body strength and endurance. Place the knees on the floor, the hands below the shoulders, and cross your feet.
2. Keeping your back straight, start bending the elbows until your chest is almost touching the floor.
3. Pause and push back to the starting position.
4. Repeat until the set is complete. No equipment. Scoring: Record the number of correctly completed push-ups.

[Time Frame: 5 minutes]

7. Muscle endurance measurement by Sit-up

The sit-up (or curl-up) is an abdominal endurance training exercise to strengthen, tighten and tone the abdominal muscles.

Technique: Squeeze your stomach, push your back flat and raise high enough for your hands to slide along your thighs to touch the tops of your knees. Don't pull with you neck or head and keep your lower back on the floor.

[Time Frame: 5 minutes]

8. Cardiorespiratory endurance measurement by Six minutes walking test

Six minutes walking test (6MWT) could be considered as a useful and reliable tool for the assessment and the follow-up of cardiorespiratory response.

Equipment required: measuring tape to mark out the track distances, stopwatch, chairs positioned for resting.

Procedure: The walking course is laid out in a 50 yard (45.72m) rectangular area (dimensions 45 x 5 yards), with cones placed at regular intervals to indicate distance walked. The aim of this test is to walk as quickly as possible for six minutes to cover as much ground as possible. Subjects are set their own pace (a preliminary trail is useful to practice pacing), and are able to stop for a rest if they desire.

[Time Frame: 6 minutes]

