VI.Each experimental group selects 2 people to supervise and remind participants of their exercise status.

VII.1 person as a walking instructor with a national second-level sports social instructor qualification certificate, 1 person as a Tai Chi Chuan skill instructor with a third-level or higher qualification certificate for Tai Chi Chuan.

VIII.Participants in each group established a contact group and were reminded before each exercise. After the exercise, they were required to record a detailed exercise log, such as exercise time and exercise content.

IX.The process of instrument testing: Before the start of data collection, all instruments and documents required for testing will be checked to ensure the validity of the instrument during the test.

X.The test environment, test instruments, and test personnel are consistent. Test each test item 3 times, take the middle value.

XI.The data after the test are all checked and processed by two researchers. 5.3 Change Management A detailed manual of the process: If the international and reference standards change during the intervention, a detailed manual containing all registry strategies, processes, and protocols, as well as a complete data dictionary listing all data elements and their definitions, will be updated regularly. This is for researchers Data collection is crucial.

Infrastructure for continuous training: personnel changes are a common problem. Specific procedures and training infrastructure should be provided at all times to cope with any unexpected changes and replacements of registered personnel or providers who regularly enter data into the record office.

The method of notifying the change: through the mobile phone group, so that the participants can report the relevant data during the exercise to the recorder in time.

6. Sample size assessment

This was based on a four-group design and the assumption of detecting a moderate effect size (partial  $\eta^2 = 0.06$ ) for a given parameter, a moderate correlation of  $r = 0.5$  almost 1 repeated measures, a level of  $\alpha = 0.05$ , and power ( $1 - \beta$ ) of 0.8 (Timmons et al., 2018). This study will be conducted as a cluster-randomized trial (CRCT) with 4 groups and 20 people per group. The ICC value of 0.01 is used in the calculation of the design effect in this study (Killip et al., 2004). As such the design effect was calculated as below:

$$DE = 1 + \rho(m-1) \quad DE = 1 + 0.01(20-1) = 1.19$$

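### The 50-yard length given for the six-minute-walk course does not match its stated 45 x 5 yard dimensions, whose perimeter is 100 yards

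*Protocol*

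**What the plan says.** Under Primary Outcome Measure, item 8 is headed "Cardiorespiratory endurance measurement by Six minutes walking test". It is the only cardiorespiratory measure among the listed outcomes. Its procedure gives the course as follows: "The walking course is laid out in a 50 yard (45.72m) rectangular area (dimensions 45 x 5 yards". Distance is read from the course itself, "with cones placed at regular intervals to indicate distance walked", and the equipment line reads "Equipment required: measuring tape to mark out the track distances, stopwatch, chairs positioned for resting". The purpose is given as "The aim of this test is to walk as quickly as possible for six minutes to cover as much ground as possible", so the result is a distance.

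The procedure does not say whether participants walk the perimeter or an out-and-back line. It does not give the spacing of the cones or the length credited for one lap. Section 5.2, item X of the Detailed Description adds a general statement on testing: "The test environment, test instruments, and test personnel are consistent".

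**The concern.** The description gives the course two sizes that do not agree if 50 yards is taken as the length of the circuit, which is the natural meaning of a course length in a distance test. A tester who lays out 45 x 5 yards and credits 50 yards per lap under-records. A tester who builds a 50-yard circuit departs from the stated dimensions.

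The outcome is measured in units of length, so the credited length enters every recorded value directly. Means, differences and confidence intervals in metres could be wrong by a constant factor and could not be compared with other data. The protocol also assigns whole classes (section 5.1.1) or whole districts (section 5.2, item II) to single arms. If crediting differed between sites, the error would therefore line up with treatment. If it differed between visits, it would appear as change over time.

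**Working it through.** **Inputs**, all from Primary Outcome Measure, item 8: stated length 50 yards (45.72 m); stated sides 45 and 5 yards. One yard is 0.9144 m.

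**1. The plan's own conversion.** 50 x 0.9144 = 45.72 m. This agrees with the protocol, so the discrepancy is not a unit slip.

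**2. What 50 yards could be in a 45 x 5 yard rectangle.**

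| Quantity | Formula | Yards | Metres |
|---|---|---|---|
| Perimeter | 2 x (45 + 5) | 100 | 91.44 |
| Half-perimeter | 45 + 5 | 50 | 45.72 |
| Long side | 45 | 45 | 41.15 |
| Diagonal | sqrt(45² + 5²) | 45.3 | 41.40 |

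The area is 45 x 5 = 225 square yards. Only the half-perimeter reproduces the stated 50 yards.

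**3. Size of a possible scoring error.** Suppose the perimeter is walked and each lap is credited as 50 yards, with part laps credited at the same rate. Then recorded / true = 50 / 100 = 0.5, and the shortfall is 91.44 - 45.72 = 45.72 m per lap. The protocol gives no expected distance, so the true distances below are assumed.

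| Assumed true distance | Laps (distance / 91.44) | Recorded (laps x 45.72) |
|---|---|---|
| 400 m | 4.37 | 200 m |
| 500 m | 5.47 | 250 m |
| 600 m | 6.56 | 300 m |

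**4. Effect on the comparison if the error is uniform.** Write the recorded distance as Y* = 0.5Y for everyone at every visit. Mean differences, standard deviations and standard errors are all multiplied by 0.5. Their ratios do not change, so F statistics, p values, standardized effects and partial eta-squared from the repeated-measures ANOVA or ANCOVA named in section 8 are unchanged. The same holds for Wald tests from a GEE with identity link. Only quantities reported in metres are wrong.

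**5. Effect if the error is not uniform.** Section 6 plans for partial eta-squared 0.06, that is f = sqrt(0.06 / 0.94) = 0.25. With an assumed within-group SD of 60 to 100 m, the planned spread (SD) of the arm means is 0.25 x 60 = 15 m to 0.25 x 100 = 25 m. Half-crediting one arm or one visit would shift its mean by 200 to 300 m over the assumed distances in step 3, far more than the effect the trial is sized to detect.

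**The case against.** A reader might infer that the course is geometrically impossible and that this primary outcome is mis-scored by a factor of two. The document supports neither inference. A 45 x 5 yard rectangle can be built, and the text attaches 50 yards to the rectangular area without calling it a lap. It may be a loose label for half the circuit.

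The halving also needs a rule of 50 yards per lap, which appears nowhere. The protocol reads distance from cones on a taped course. If the cones stand at taped distances along the walked path, recorded distances are right whatever the label says.

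A reader might also infer that the error is confounded with arm. That would require staff to resolve the discrepancy differently across sites or visits. Against this, section 5.2 calls for consistent environment, instruments and personnel (item X) and has two researchers check the data (item XI). Sections 1 and 2 of the Detailed Description call for trained measurers and describe range and consistency checks, which could reveal a twofold gap.

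All of this limits how far the point reaches, but it does not remove the discrepancy. Cones at an unstated interval do not show which length is credited. Consistent conditions make mixed readings less likely, yet they do not prevent everyone from making the same error.

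**Conclusion.** The stated length and the stated dimensions disagree by a factor of two when 50 yards is read as the circuit: 50 yards (45.72 m) against 100 yards (91.44 m). Nothing else in the protocol resolves this. It is a contradictory figure in the definition of a primary outcome, not a detail that could be left to an analysis plan.

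The consequence is conditional. Recorded distances are halved only if the 45 x 5 yard perimeter is walked and 50 yards is credited per lap. In that case the metres are wrong. Between-group tests still stand if the error is uniform, and are biased if it varies by site or visit. The document does not show that either occurred. The arithmetic on the course rests on no assumption. The illustrations rest on assumed walking distances of 400 to 600 m and an assumed SD of 60 to 100 m.

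Severity is minor to moderate. The point concerns one of eight listed primary outcomes and affects no alpha, power or sample-size figure.

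**What to change.** The record shows an actual start in July 2021 and 100 participants actually enrolled, so the first step is to establish what was done.

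1. Confirm by tape, at every test site, which course was used at baseline and what length was credited per lap or per cone.
2. State in item 8 the dimensions, walked path, cone spacing and credited lap length of that course, so that they agree. If 45 x 5 yards was laid out and its perimeter walked, the lap is 100 yards (91.44 m).
3. Keep that same course at every site and visit. A rectangle of 20 x 5 yards would have a 50-yard perimeter, but moving to it now would change the number of turns and weaken comparability with baseline.
4. If a wrong lap length was credited, correct the recorded distances by the known factor (100 / 50 = 2 for perimeter laps credited as 50 yards). If part laps were measured separately, add 45.72 m for each complete lap instead. Apply the correction only to the sites and visits concerned, and report it.

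The cost is one line of text and a tape check, plus a rescaling of existing records if the check shows it is needed.

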#### Secondary Outcome Measure:

9. BMI (body mass index) measurement by Height and weight

Height and weight can measure human body shape. The formula is  $BMI = \frac{kg}{m^2}$  where kg is a person's weight in kilograms and m^2 is their height in metres squared. The healthy range is 18.5 to 24.9. The WHO regards a BMI of less than 18.5 as underweight and may indicate malnutrition, an eating disorder, or other health problems, while a BMI equal to or greater than 25 is considered overweight and above 30 is considered obese (World Health Organization (WHO), 2006).

[Time Frame: 2 minutes]

10. Balance measurement by Tinetti-test

The Tinetti-test (Tinetti et al., 1986) was published by Mary Tinetti (Yale University) to assess the gait and balance in older adults (Berg et al., 1992) and to assess perception of balance and stability during activities of daily living and fear of falling.

The test requires a hard armless chair, a stopwatch and also, a 15 feet even and uniform walkway. It has 2 sections: one assesses balance abilities in a chair and also in standing; the other assesses dynamic balance during gait on a 15 feet even walkway. The patient is to sit in an armless chair and will be asked to rise up and stay standing. The patient will then turn 360° and then sit back down. This is to test the patients' balance.

[Time Frame: 5 minutes]

11. Resting heart rate (RHR)

Resting heart rate (RHR) is the number of times your heart beats per minute (bpm) while at complete rest (Kolloch et al., 2008).

A healthy resting heart rate for adults is 60 to 80 bpm. Adults with a high level of fitness can have a resting heart rate below 60. Some elite endurance athletes have a resting heart rate below 40 (Almeida & Araújo, 2003).

[Time Frame: 1 minutes]

12. Blood Pressure

Measuring blood pressure is important for accurately judging values and screening high blood pressure.

When the blood pressure of 40-70-year-old people is in the range of 115/75-185/115mmHg, the risk of cardiovascular disease doubles for every 20mmHg increase in systolic blood pressure or 10mmHg increase in diastolic blood pressure. According to JNC7, a systolic blood pressure between 120~139mmHg or a diastolic blood pressure between 80~89mmHg belongs to prehypertension.

[Time Frame: 1 minutes]

#### Other Pre-specified Outcome Measures:

13. Quality of life measurement by SWLS

The Satisfaction With Life Scale (SWLS) is a 7-point Likert style response scale to measure Quality of life.

Scoring A total score is calculated by adding up the scores for each item. The possible range of scores is 5-35, with a score of 20 representing a neutral point on the scale. Scores between 5-9 indicate the respondent is extremely dissatisfied with life, whereas scores between 31-35 indicate the respondent is extremely satisfied. The following chart provides cutoff scores to be used as benchmarks.

[Time Frame: 5 minutes]

## Eligibility

Minimum Age: 60 Years

Maximum Age: 69 Years

Sex: Female

Gender Based: Yes

Chinese women

Accepts Healthy Volunteers: Yes

Criteria: Inclusion Criteria:

- Less than 30 minutes of moderate-intensity physical activity per week.
- Through the screening of the PAR-Q questionnaire (If one of the questions is answered "yes", the potential participants will be excluded) and the basic physical examination of the elderly by doctors, to determine that the elderly can complete exercise independently.

Exclusion Criteria:

- Subjects participated in other sports training at the same time.
- If the subjects have recently (less than one year) undergone surgery on the knee, elbow, shoulder, etc., has a history of rheumatoid disease or neurological disease, and is still receiving treatment, it will be excluded.
- If the subjects answered "yes" to the PAR-Q questionnaire.

